#### Sample Size

As our main analyses focus on patients assessed in person, our sample size calculation is based solely on their numbers. We estimate that the rate of return visit for ambulatory emergency conditions varies from 1% to 13% depending on the care setting [17,110,111]. To account for the potential similarity in outcomes among individuals in each of the 15 clusters, we assumed a realistic intracluster correlation of =0.02 based on previous studies and applied a correction to inflate our sample size calculation [112,113]. Using data from Campbell et al [28], at least 1485 patients (approximately 99 per cluster) will be needed to reveal a 5% difference in the proportion of return visits within 72 hours (eg, 5% vs 10%), assuming a 20% loss to follow-up and at least 30 participants per condition, based on multivariate logistic regression power analysis, type I error (α) at .05, and power at 80% (1−β). Assuming 240 recruitment days over a year at each site and the recruitment of at least 1 to 2 patients per day, our final cohort should include over 4000 patients and reach the minimal sample size in both participating provinces, which will allow for more robust comparisons and analyses.

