## Methods

### Phase 1: A Time-Driven Activity-Based Costing Method Study

#### Setting

A time-driven activity-based costing study will first be performed for fiscal year April 1, 2021, to March 31, 2022. We shall estimate the cost of care processes administered by care providers (Objective 1) in 3 different models of ambulatory emergency care in Québec and Ontario: (1) discontinuous care in the ED (by physicians unfamiliar with the patients); (2) discontinuous care in a walk-in clinic (by physicians unfamiliar with the patients); and (3) continuous care in primary care clinic (patients attached to a primary care practice, seen by their family physician or a colleague on a same-day appointment for urgent needs).

We have confirmed the participation of 14 of the 15 planned patient recruitment sites (ED 5/5, walk-in 5/5, primary care 4/5; Multimedia Appendix 1). They have been selected in different types of urban areas, including small (Joliette), medium (Kingston), large (Québec City, Ottawa), and metropolitan (Montreal) cities. In each participating region, an ED will be paired with a nearby walk-in clinic and primary care practice. We are currently securing our final additional clinic in Ottawa with the help of BeACCoN (Better Access and Care for Complex Needs), a provincial primary care research network.

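### With 5 sites per setting and the plan's own ICC of 0.02, 1485 patients give about 38% power, not 80%, for a pairwise comparison of 5% vs 10% return visits

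*Protocol article*

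**What the plan says.** The Sample Size section of the protocol article (Methods, Phase 2) states that "at least 1485 patients (approximately 99 per cluster) will be needed to reveal a 5% difference in the proportion of return visits". The interval is 72 hours, the example given is 5% against 10%, alpha is .05 and power is 80%. It names multivariate logistic regression as the basis of the power analysis. On clustering it says "we assumed a realistic intracluster correlation of =0.02 based on previous studies" and that the authors "applied a correction to inflate our sample size calculation", to allow for similar outcomes among "individuals in each of the 15 clusters". The figure is given "assuming a 20% loss to follow-up and at least 30 participants per condition".

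The section closes by expecting more than the minimum: "our final cohort should include over 4000 patients and reach the minimal sample size in both participating provinces".

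The Setting section (Phase 1) shows how sites divide between settings: "14 of the 15 planned patient recruitment sites (ED 5/5, walk-in 5/5, primary care 4/5"), so 5 sites are planned per setting. The Statistical Analysis section compares the three settings in multilevel models with random intercepts for province and practice unit. Care setting is the only independent variable in the weighted outcome models.

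**The concern.** Every site belongs to one setting, so the exposure of interest varies only between sites. The information on a setting contrast is then limited by the number of sites as well as by the number of patients. With 79 evaluable patients per site, even an ICC of 0.02 more than doubles the variance. A total of 1485 looks too small to contain that inflation.

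Return visits are a primary outcome, and the 72-hour figure is one axis of the planned value graphic. At about 38% power, a true doubling of return visits from 5% to 10% would be missed about 6 times in 10. A reader who relies on the stated 80% would misjudge what the study can show, both overall and by province.

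**Working it through.** **Inputs.** From Sample Size: 1485 patients, 99 per site, 15 sites, ICC 0.02, 20% loss, 5% vs 10%, alpha .05, power 80%. From Setting: 5 sites per setting. Sidedness is not stated; two-sided is assumed.

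**Step 1: patients needed without clustering.** With pooled variance and mean proportion 0.075:

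n = [1.96·√(2·0.075·0.925) + 0.842·√(0.05·0.95 + 0.10·0.90)]² / 0.05² = (0.730 + 0.312)² / 0.0025 ≈ 434.4, so 435 evaluable per setting.

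**Step 2: can 1485 be reproduced?**
- Three settings, no clustering: 3 × 435 = 1305; divided by 0.8, 1632.
- Two groups only, no clustering: 870; divided by 0.8, 1088.
- Three settings, design effect 2.564 (79.2 evaluable per site): 1305 × 2.564 / 0.8 ≈ 4183.
- Three settings, design effect 2.96 (99 per site): 1305 × 2.96 / 0.8 ≈ 4829.

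One-sided tests, a continuity correction, Bonferroni adjustment and logistic-regression sample size formulas were also tried. None that uses the stated ICC gives 1485. The nearest values leave the ICC out and need an input that the plan does not state: 1450 (two groups, alpha/3) and 1461 (logistic formula, exposure prevalence 1/3, R² 0.2).

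**Step 3: what 1485 delivers.** Evaluable patients: 1485 × 0.8 = 1188, or 396 per setting and 79.2 per site.
- At ICC 0, 396 per setting gives 76% power. With no loss either, 495 per setting would give 85%.
- At ICC 0.02, the design effect is 1 + (79.2 − 1) × 0.02 = 2.564, and the effective size is 396 / 2.564 ≈ 154 per setting.
- Power = Φ{[0.05 − 1.96·√(0.13875/154.4)] / √(0.1375/154.4)} = Φ(−0.293) ≈ 38%.
- With no loss: design effect 2.96, effective size 167, power 41%.
- With a small-cluster t reference: 34% on 12 df and 31% on 8 df. A beta-binomial simulation gave 33% with a cluster-level t-test and 39% with a z-test.

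**Step 4: more patients at the same sites.** If the whole ICC is between sites, effective size per setting is 5m / [1 + (m − 1) × 0.02], which cannot exceed 5 / 0.02 = 250.

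| Patients enrolled | Effective per setting | Power, 5% vs 10% | Detectable at 80% power |
|---|---|---|---|
| 1485 | 154 | 38% | 5% vs 14.4% |
| 4000 | 203 | 48% | 5% vs 12.9% |
| Unlimited | 250 | 56% | 5% vs 12.0% |

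The first two rows allow for the 20% loss. Reaching 435 effective patients needs more than 435 × 0.02 = 8.7 sites per setting whatever the site size, and 435 × 2.564 / 79.2 ≈ 14.1 at the planned site size.

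**Step 5: province.** The figure of 1485 is tied to 15 clusters. The 15 sites are shared between two provinces, so each has fewer, and the ceiling on effective size per setting falls below 250. For illustration, assume 2 sites per setting in Ontario, as the named cities suggest. The ceiling is then 2 / 0.02 = 100. Enrolling 1485 there gives about 80 effective per setting after loss and 22% power, and the limit is 27%.

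**The case against.** **The contrast is only an example.** The plan offers 5% vs 10% as an illustration and quotes return-visit rates from 1% to 13%. A 5-point difference at lower rates is easier to detect: 1% vs 6% has 67% power at 1485, 79% at 4000 and a limit of 86%. At the upper end, 8% vs 13% has 30% at 1485. So the 56% limit belongs to the 5% vs 10% pair, but neither end of the range reaches 80% at 1485.

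**The test need not be pairwise.** One setting against the other two pooled gives 45% or 53% at 1485, depending on which side has the lower rate, with limits of 66% and 72%. A two-degree-of-freedom overall test has a limit of at most 64%. These are better than pairwise, but all stay below 80% two-sided.

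**Part of the ICC may be shared.** Sites are grouped by region, and the model has a province intercept. Variance shared within a region or province would largely cancel from setting contrasts if modelled. The plan gives no split. If half of 0.02 were shared (an assumption), power would be 52% at 1485 and 70% at 4000, with a limit of 85%. This stands as a reason to qualify the limit. It does not rescue 1485.

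**The analysis already allows for clustering.** True: the planned model has practice-unit intercepts, so inference is not at issue. Such a model carries the variance penalty; it does not remove it.

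**Conclusion.** The stated 80% is wrong on the plan's own inputs. Pairwise two-sided power for 5% vs 10% is about 38% at 1485 patients (about 33% with a small-cluster t reference, 41% with no loss) and about 48% at 4000. The shortfall exists even at ICC 0, where power is 76%. These figures assume equal site sizes, 5 sites per setting and an ICC of 0.02 wholly between sites. They allow nothing for precision lost to overlap weighting, which would lower power further.

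Four stronger readings are tempting and not supported:
- That no enrolment at 15 sites could ever give 80%. This holds for 5% vs 10% under the assumptions named, not for every 5-point difference or every division of the ICC.
- That a cohort above 4000 is unattainable. At 1 to 2 patients per day, 240 days and 15 sites, recruitment spans 3600 to 7200, which includes it.
- That the authors intend to read a non-significant result as equal quality. The plan speaks only of revealing a difference.
- That Ontario's power is known. The appendix listing sites by province is not shown, so the 22% to 27% rests on an assumed 2 sites per setting. The general point, that 1485 within one province lacks the stated power, does not depend on that split.

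**What to change.** In Sample Size:

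1. Replace the 80% claim. State that, with 5 sites per setting, ICC 0.02 taken as wholly between sites, 20% loss and a two-sided alpha of .05, 1485 patients give about 38% pairwise power for 5% vs 10% and 80% power for about 5% vs 14%. State that 4000 patients give about 48% and detect about 5% vs 13%.
2. Add that, under these assumptions, more patients at the same 15 sites do not restore 80% power for 5% vs 10%. If the authors rely on another contrast or a smaller site-specific ICC, they should state it and show the derivation.
3. Delete the claim that the minimum is reached in both provinces. Any power quoted for Ontario alone should be labelled as resting on an assumed 2 sites per setting, unless the site list confirms it.
4. Say that the return-visit contrast will be presented with its cluster-adjusted 95% CI, which the planned multilevel model can supply.

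The cost is wording and a less favourable stated power. No patients or sites are added, and the planned model is unchanged.

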#### Statistical Analysis

All main analyses will be conducted primarily on participants assessed in person in any of the care settings. Participants assessed by telemedicine will be analyzed and compared separately between sites where it is implemented. The value delivered at each participating site and on average in each care setting type will be illustrated with an operational effectiveness graphic [114]. Adjusted costs of care for acute ambulatory respiratory conditions will be plotted on the x-axis and adjusted return visits within 72 hours on the y-axis. Points closest to 0 on both axes represent the highest value of care (Multimedia Appendix 6). Indeed, the lower the return visit proportion and cost of care, the higher the value of care. Similar graphics will be used for patient-centered outcome measures. To compare EDs, walk-in clinics, and primary care physician practices, multilevel generalized linear models will be used with probability distributions adapted to the outcome under evaluation. To adjust for confounding (differences in case mix between care settings), an overlap weights approach [115,116] will be used, wherein each individual receives a weight factor that is proportional to the inverse of the probability of choosing a particular setting. Subjects that differ fundamentally between settings are attributed a weight of 0 and are thus excluded. This approach is of the greatest interest when groups are initially very different [116]. Intuitively, overlap weights create a pseudopopulation for which treatment is independent of measured confounders, thus mimicking a randomized trial of those confounders. Overlap weights have been shown to be more robust than conventional inverse probability weighting and matching based on propensity scores [115]. The weights will be estimated using a multinomial logistic regression model in which the dependent variable is the chosen care setting and independent variables are potential confounders or risk factors [117] for the outcomes identified in the literature: age [118,119], sex and gender [118,120], ethnicity [118,121-123], registration with a family physician [20,124], comorbidities (the Charlson index; number of regular medications) [118,125,126], asthma, FEV_1_ among patients with asthma, the Canadian deprivation index [127-129], patient perception of illness severity [130], and vital signs [131-135] as proxies for severity. The same independent variables will be used to adjust for differences in case mix between settings in the telemedicine cohort, excluding vital signs and FEV_1_. Multiple imputation will be considered as a possible means to adjust for these variables in this cohort. Overlap weights will be calculated using the values predicted by this model. We shall verify that the care setting groups are comparable according to the measured confounders after weighting by computing standardized mean differences. Differences below 10% will be considered to indicate good balance [117]. If residual imbalances are present, the weighting model will be revised. Once an appropriate balance is achieved, separate models for each outcome will be fitted to the weighted data, for which the care setting will be the only independent variable. The robustness of results with respect to unmeasured confounding will be assessed using the E-value [136,137]. Clustering by setting (eg, province, practice unit) will be taken into account using multilevel modeling (random intercept on province and practice unit). Reported cost estimates will be calculated with item-specific standardized costs (eg, Québec and Ontario average nurse unit cost). Patients referred to the ED from a participating outpatient facility but discharged home after ED assessment will be analyzed in the care setting group where they first presented, and the ED referral will be considered as a return visit. The costs of any return visits and admissions up to 7 days after the initial visit will be estimated separately and attributed to the care setting where the initial visit took place. Results of the 3 questionnaires from the patient perspective will be reported as proportions (PREM), mean costs (CoPaQ), and median scores (PROM-ED) and adjusted using the overlap weights approach. As patients seek care for symptoms, subanalysis based on presenting complaints instead of discharge diagnosis will be conducted to provide meaningful patient-oriented results. Other subanalyses will evaluate which patient profile (eg, gender [120], motivation for choosing a facility), and institutional characteristics (eg, access to x-ray) predict high quality and low costs, keeping in mind that our value assessment might not yield similar results for all subgroups or even within a group of patients with the same diagnosis. Statistical differences will be assessed with a significance threshold set at .05.

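### The value graphic promises adjusted points for each site, but the adjustment described balances only the three care settings, so case mix between sites of one type stays in the site points

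*Protocol article*

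**What the plan says.** All of the following is in the Statistical Analysis section of the protocol article unless noted.

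- **What is plotted.** "The value delivered at each participating site and on average in each care setting type will be illustrated with an operational effectiveness graphic". The horizontal axis is defined by "Adjusted costs of care for acute ambulatory respiratory conditions will be plotted on the x-axis" and the vertical axis by "adjusted return visits within 72 hours on the y-axis". The reading rule is "Points closest to 0 on both axes represent the highest value of care".
- **What the adjustment is for.** "To adjust for confounding (differences in case mix between care settings), an overlap weights approach" is the only adjustment method named for in-person patients.
- **How the weights are built.** They come from a "multinomial logistic regression model in which the dependent variable is the chosen care setting". Balance is then checked by standardized mean differences between the care setting groups, with 10% as the limit.
- **What the outcome models contain.** After weighting, "separate models for each outcome will be fitted to the weighted data, for which the care setting will be the only independent variable". Random intercepts for province and practice unit account for clustering.
- **Where the sites are.** Under Setting (Phase 1): "They have been selected in different types of urban areas, including small (Joliette), medium (Kingston), large (Québec City, Ottawa), and metropolitan (Montreal) cities". There are 15 planned sites, five of each type, and each emergency department is paired with a nearby walk-in clinic and primary care practice.

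**The concern.** A propensity model for emergency department versus walk-in clinic versus primary care gives weights that align three pooled groups. It contains no information on which site of a given type a patient attended, so it has no mechanism to align the five sites within a type. The outcome model has no patient covariate that could do this afterwards. An older or sicker intake at one emergency department would thus move that site's point up and to the right on axes that the reader is told are adjusted, and the reading rule would call this lower value.

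The stake is how the site points are read. The Discussion hopes that the study will support valid comparisons and quality improvement. A site point that mixes case mix with performance does not serve that aim, and the balance check as planned cannot reveal the problem.

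**Working it through.** **Step 1. Follow the adjustment chain.** The document gives no figure to reproduce here, so the check is structural.

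| Element | Level at which it works | Balances sites of one type? |
|---|---|---|
| Overlap weights | 3 settings | No |
| 10% balance check | 3 settings | No, and cannot detect it |
| Fixed part of outcome model | 3 settings, no patient covariate | No |
| Practice-unit random intercept | 15 sites | No: it absorbs case mix and performance together |
| Standardized costs (Intermediate Outputs of Phase 1) | Unit prices | No: removes price effects only |
| Sensitivity analyses | Effects of the 3 settings | No |
| Graphic | 15 sites and 3 settings | Promises adjusted points at both levels |

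**Step 2. Show the mechanism.** Assumptions, none of them from the document: one severity covariate; setting means +0.4, 0 and −0.4 SD; log-odds slope 0.7; no true effect of site or setting; five sites per setting with means spread evenly over ±0.25, ±0.5 or ±0.75 SD. With 20,000 patients per site, the standard error of a site proportion near 7.5% is √(0.075 × 0.925 / 20,000) ≈ 0.2 points, so sampling noise is small.

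In the middle scenario the weights do their own job. Crude return rates of 9.6, 7.5 and 5.7% by setting become 7.4, 7.4 and 7.2%, and weighted covariate means agree to within 0.001 SD. Within the emergency departments, weighted site means still run from −0.43 to +0.51 SD, against the ±0.5 built in.

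| Spread of site means within type | Weighted return rate over 15 sites | False spread | With site and covariate in the model, standardized |
|---|---|---|---|
| ±0.25 SD | 6.2 to 8.5% | 2.3 points | 7.2 to 7.7% |
| ±0.5 SD | 5.3 to 9.9% | 4.6 points | 7.3 to 7.9% |
| ±0.75 SD | 4.3 to 11.8% | 7.5 points | 7.6 to 8.0% |

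A second simulation, with four covariates and random site means of SD 0.2, 0.3 or 0.5, gave median expected spreads of 3.8, 5.4 and 8.4 points. With weaker covariate effects (log-odds 0.4 for each of three covariates), the spreads were about 3, 4 and 7 points, against 1 to 2 points when sites had the same mix.

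**Step 3. Allow for the random intercept.** If site points were predicted random intercepts, the share of a site's deviation that is kept is about m × ICC / (1 + (m − 1) × ICC). The Sample Size section gives ICC 0.02 and 99 patients per cluster: 1.98 / 2.96 = 0.67. After 20% loss, m is about 79: 1.58 / 2.56 = 0.62. Shrinkage therefore removes roughly a third of the distortion, and the same share of any real difference.

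**Step 4. Compare with chance.** Completers per site are 1485 × 0.8 / 15 ≈ 79 at the minimum size and 4000 × 0.8 / 15 ≈ 213 at the hoped-for size. For 15 identical sites at an assumed return rate of 7.5%, binomial sampling alone gives a median observed range of about 10 points at 79 per site (7.6 at a 5% rate, 11.4 at 10%) and about 6 points at 214 per site. At the minimum size, the false spreads in Step 2 are comparable to chance or below it. At the larger size, the stronger scenarios exceed it.

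**The case against.** The strongest reply is that the link is inferred. The weights and the covariate-free models are introduced for comparing the three settings, and the article nowhere says that the site points come from them. A condensed article may leave the site method to a fuller plan, and the team's pilot did report covariate-adjusted mean costs (Table 1 footnote). This stands in part: a separate site-level method may exist. But the article is not silent. It fixes the weighting model, the balance criterion and the outcome model, promises adjusted site points, and names no other route to them.

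Several limits stand in full. The objectives compare settings, and site value is only illustrated. Pairing within regions means that regional mix is partly shared across types. Eligibility (ambulatory, discharged home, no ambulance, no long-term or palliative care) and the exclusion of night patients narrow case mix. At the minimum sample size, chance alone would scatter the points widely.

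A reader might go further and infer that in-person sites will be formally tested or ranked, with an inflated false-positive rate, or that named sites will be exposed. The article plans no such test or ranking and does not say that points will be labelled by site, so no error rate can be attached to this display. A reader might also infer that the main comparison is biased. It is not on this account: the weights address the setting contrast, which is what that comparison uses.

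**Conclusion.** The point holds for the site-level points of the value graphic. As written, the adjustment cannot deliver site points adjusted for case mix between sites of the same type, and the 10% balance check would not show the failure. The direction of the argument follows from the text alone.

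The size does not. False spreads of roughly 2 to 8 percentage points in 72-hour return visits rest on assumed differences between sites and assumed covariate effects. At about 79 completers per site they are comparable to or below chance variation, and they matter more as enrolment approaches 4000. No distortion of cost was quantified; the same reasoning applies, because standardized unit costs do not remove differences in patient need. The three-setting contrast is unaffected. This is a correction worth making before the graphic is produced, not a threat to the main result.

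**What to change.** For the site points, fit for each plotted outcome a model with the listed patient covariates, care setting and a practice-unit random intercept. Plot each site's prediction with a 95% interval, standardized to the overlap-weighted cohort, which is the population behind the setting averages. Using another reference population would put two targets on one graph, and site points would not line up with their setting's point.

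Reduce or penalize the covariate set if events are few. At the minimum size and an assumed 7.5% return rate there are about 1485 × 0.8 × 0.075 ≈ 89 events in all, or about 6 per site.

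If this model is not wanted, either plot only the three setting averages or label the site points as not adjusted for case mix between sites of the same type. In every case, state that the 10% balance check covers setting contrasts only.

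The cost is one additional model per plotted outcome, using data already to be collected. The downsides are reliance on an outcome model for the site points and shrinkage of those points toward the mean.

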#### Selection of Participants

We shall include patients (1) aged 18 years and older; (2) seen in person or via telemedicine in an ED, a walk-in clinic, or the primary care practice where they are registered; (3) ambulatory during the entire visit or consultation; and (4) discharged home with a diagnosis of URTI, sinusitis, otitis media, pharyngitis, tonsillitis, bronchitis, influenza-like illness, pneumonia, acute asthma, or acute exacerbation of COPD. We shall exclude patients (1) transported by ambulance, (2) not covered by the provincial health insurance plan, (3) having consulted for a similar problem in the previous 30 days as patients with refractory diseases representing a population with different care needs, (4) living in a long-term health care facility or incarcerated, or (5) receiving palliative care.

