#### Outcome Measures

A value-based comparative assessment requires the simultaneous evaluation of health outcomes and costs. Our outcome measures were chosen from a guideline on the assessment of ED performance [90] and recent literature on patient experience assessment (Table 2) [91-95]. The initial visit, from arrival at a participating site to discharge, represents the unit of analysis for all outcome measures; however, the health system or patient costs incurred during the following week will be estimated and added to the cost of the initial visit. For participants assessed in person, the outcome will be scored per care setting and further stratified per discharge diagnosis and by province, using institution-specific costs for interprovincial cost comparisons. We will analyze the same outcome measures separately in the case of patients evaluated by telemedicine, as missing data (eg, vital signs) will prevent us from adjusting for the severity of their illness.

**Table 2 table2:** Main study outcomes.

Outcome		Definition	Source

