**Primary**			
	Incidence of return visit (O^a^)	Proportion of patients returning to any ED^b^ or outpatient clinic at 72 hours and 7 days after the initial visit [83,96-99]. An adjudication committee will review records of return visits to classify them as planned or unplanned and avoidable or unavoidable.	Follow-up call at 10 days
	Mean cost of care−the Ministry of Health perspective (C^c^)	The cost per care episode calculated by summing the costs of all care processes delivered to a patient during the initial visit plus the costs of return visits and admissions at 72 hours and 7 days.	Electronic medical records and provincial billing databases

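### Scoring a clinic patient's same-episode ED referral as a return visit adds an event to the primary outcome that only the two clinic groups can have

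*Protocol article*

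**What the plan says.** The rule is in Phase 2, Statistical Analysis. It covers this group: "Patients referred to the ED from a participating outpatient facility but discharged home after ED assessment". Such patients "will be analyzed in the care setting group where they first presented, and the ED referral will be considered as a return visit".

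Four other statements bear on it:

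- Outcome Measures defines the index event: "The initial visit, from arrival at a participating site to discharge, represents the unit of analysis for all outcome measures".
- Table 2 defines the first primary outcome as the proportion of patients returning to any ED "or outpatient clinic at 72 hours and 7 days after the initial visit". It adds: "An adjudication committee will review records of return visits to classify them as planned or unplanned and avoidable or unavoidable". The outcome is not restricted to any of those classes.
- Selection of Participants requires that a patient be "discharged home with a diagnosis of URTI" or one of the other listed conditions.
- The value graphic plots adjusted 72-hour return visits against adjusted cost, on the principle that "the lower the return visit proportion and cost of care, the higher the value of care".

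The cost of a return visit within 7 days is charged to the setting of the initial visit.

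**The concern.** A patient who presents first to the ED cannot be referred to the ED. Statistical Analysis names access to x-ray as an institutional characteristic that may matter. A clinic patient sent to the ED for a film the clinic cannot take scores a return; an ED patient who has the same film on site does not. The same clinical need in the same illness episode is thus an outcome event in two settings and part of the index visit in the third.

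The overlap weights cannot correct this. They balance patient characteristics across settings and do not touch an outcome whose content differs by setting.

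The 72-hour return proportion is a primary outcome, the basis of the sample size and the vertical axis of the value graphic. A referral also adds cost to the clinic's episode, so it moves the clinic unfavourably on both axes. A higher clinic rate could then be read as more patients coming back after discharge when it partly reflects how often clinics complete an episode by sending the patient on.

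**Working it through.** **1. Reading the definitions together.** The question is what ends the initial visit.

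- If discharge in Outcome Measures means discharge home, as in Selection of Participants, the referred patient's initial visit ends when the ED sends the patient home. The ED assessment lies inside the initial visit and cannot be a return after it. The referral rule then conflicts with Outcome Measures and Table 2.
- If discharge means leaving the first site, the ED attendance follows the initial visit and the rule fits both. The patient then satisfies the discharged-home criterion only through the ED's discharge.

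The text does not choose between the two.

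**2. Inputs for the size of the effect.**

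- From Sample Size: target difference 5 points at 72 hours (for example 5% vs 10%); return rates from 1% to 13%; intracluster correlation 0.02; loss 20%; alpha .05; power 80%; 1485 patients, about 99 per cluster.
- From the Phase 1 Setting section: five planned sites per setting, taken as 1485/3 = 495 per setting.
- Assumed, because the documents give no figure: r, the share of clinic patients with a same-episode ED referral, from 1% to 5%.

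The standard two-sided formula for 5% vs 10% gives 435 per setting. Three settings with 20% loss need 3 × 435/0.8, about 1632, before any allowance for clustering. I could not validly reproduce 1485. That is a separate matter and does not bear on this point.

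**3. Added clinic proportion.** With p the return rate without the rule, and referral independent of later return:

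clinic rate = r + (1 − r)p, so added = r(1 − p).

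| r | clinic rate at p = 5% | added (points) |
|---|---|---|
| 1% | 5.95% | 0.95 |
| 2% | 6.90% | 1.90 |
| 3% | 7.85% | 2.85 |
| 5% | 9.75% | 4.75 |

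The choice of p matters little. Over the plan's range of 1% to 13%, r = 2% adds 0.02 × 0.99 = 1.98 down to 0.02 × 0.87 = 1.74 points, and r = 5% adds 4.95 down to 4.35. Independence matters more: if a fraction q of referred patients would have had another return anyway, the addition is r(1 − q), anywhere from 0 to r. At p = 5%, the full 5 points would need r = 0.05/0.95 = 5.3%.

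**4. What that does to the test.** Take equal underlying rates of 5% and compare one clinic group with the ED group.

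- Evaluable per setting: 495 × 0.8 = 396, or 396/5 = 79.2 per site.
- Design effect: 1 + (79.2 − 1) × 0.02 = 2.564. Effective size: 396/2.564 = 154.
- Chance of a significantly higher clinic rate: Φ(Δ/SE − 1.96), with SE = √(2p̄(1 − p̄)/n).
- For r = 2%: Δ = 0.019, p̄ = 0.0595, SE = 0.0269, giving Φ(0.71 − 1.96), about 11%.
- For r = 3% and 5%: about 17% and 36%. With no shift, about 2.5% would be expected in that direction. If clustering is ignored, the three figures are 20%, 37% and 73%.

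**5. The rule can also hide a difference.** If true rates are ED 10% and clinic 5%, with 435 per setting and no clustering, power falls from 80% to about 60% (r = 1%), 38% (r = 2%) and 20% (r = 3%).

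**The case against.** The best defence is that this is an open, prespecified first-contact rule. The study compares the settings where care begins, and needing a second facility for the same illness is a real consequence of starting at a clinic. The Introduction raises this concern itself when it notes that walk-in clinics may duplicate care. A setting's capacity to finish the episode is arguably part of its value, and taking these referrals out of the main comparison altogether would change the estimand in the clinics' favour. That stands, and it is why the rule need not be replaced.

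A reader might infer two stronger points that the article does not support.

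- That the rule flatly contradicts the definition of the initial visit. It does so only if discharge means discharge home, and Outcome Measures does not say that.
- That ED patients are shielded from the endpoint. They are not: any later ED or clinic visit counts for them, including one made on referral. Only the same-episode ED referral is closed to them, so the net bias over all return visits is not established.

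It is also fair to say that the adjudication committee could help to identify these events, and that the full outcome list (Multimedia Appendix 5) and any analysis plan are not at hand. But planned versus unplanned and avoidable versus unavoidable do not isolate same-episode referrals. The primary outcome is not limited to any of those classes, and none of the listed sensitivity analyses separates referrals. The point rests on a scoring rule the article does fix, not on detail it leaves out.

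**Conclusion.** The point holds in a limited form. The rule works in one direction: it can raise the return-visit proportion in the two clinic groups only, so an ED-versus-clinic difference cannot be read simply as a difference in return after discharge. The definitions are ambiguous and need reconciling; a contradiction is not established.

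The size is conditional. At 5% underlying returns and independence, referral shares of 1% to 5% add 0.95 to 4.75 points. The figure at 5% comes close to the whole target difference, and a reader might take it as the expected bias. It is only the top of an assumed range: the documents give no referral rate, and the rule is confined to ambulatory patients who are sent home after ED assessment. At 2% the shift is 1.9 points. That is still large enough to change what a 5-point contrast can be taken to show.

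**What to change.** 1. State what ends the initial visit for a patient referred from a clinic to the ED, and make Selection of Participants, Outcome Measures, Table 2 and the referral rule in Statistical Analysis agree with it.
2. Keep analysis by setting of first presentation, and keep the referral's cost in the episode cost.
3. Record same-episode ED referral as its own component, separate from return after discharge home.
4. Prespecify the primary return-visit comparison and the value graphic both with and without that component.
5. Qualify any conclusion about settings that depends on which version is used.

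This is a cheap improvement. It costs one indicator and one extra model run on data the study already plans to collect. The downside is a second version of the primary result to report and explain.
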